#### **9.4. Study population:**

Patients older than 18 years and younger than 50 with indeterminate chronic CD attending the PCC will be enrolled equally and randomly into the four study groups. According to PCC guidelines, patients older than 50 are not eligible for antichagasic therapy. For subject selection, see below. The choice of this target population for CD is primarily due to the unmet medical need for a new, safe and effective treatment for chronic indeterminate CD.

#### **9.5. Duration of the study and duration of subject participation:**

The total duration of patients' participation in the study will be twelve months, considering two weeks for screening and evaluation according to PCC guidelines and eight weeks of treatment with the antichagasic drugs. The administration of ATO and placebo will continue for an additional eight weeks in their respective groups. There will be follow-up visits up to 12 months after the start of treatment (see appendix for a graphical presentation of the study design).

Following voluntary written informed consent, patients will begin a 14-day evaluation phase. Once the patient is randomized and treatments are initiated, they will have follow-up visits during the treatment phase of the study on days 30, 60, 120, and 180, with a two-week rest period or until normalization of liver enzyme levels ( $\pm$  four-day allowable window), and three visits after the end of treatment (EOT) on days 180, 240 and 360 ( $\pm$  14-day allowable window). In addition, patients will be advised to return on any day during the follow-up period if they have any medical incidents or AEs.

Recruitment is expected to be completed within 24 months from the start of recruitment. Therefore, the time frame between the first patient entering (FPI) and the last patient leaving (LPO) is 36 months. However, the total duration of the study is estimated at 48 months, from the initiation phase to the final study report.

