#### **7.1.4. Treatment of chronic chagasic cardiomyopathy and strategies of improvement:**

In Chile, etiologic treatment of CD is with 5-10 mg/kg/day of nifurtimox (NFX) or 5 mg/kg/day of benznidazole (BZD) for 60 days (MINSAL, 2017). All patients should receive antichagasic treatment without exclusion or delay, except during pregnancy and lactation, although there is recent evidence suggesting that NFX may be safe in these conditions (Moroni et al., 2019). Also, hypersensitivity to trypanocidal drugs excludes its use. Other exclusions are severe renal, hepatic, or cardiac disease, including CCC with structural compromise, alcoholism (Antabuse effect of NFX), and severe megacolon or megaesophagus (MINSAL, 2017).

Treatment of CD is associated with an increased risk of serious adverse events (AEs), with a mean incidence of 16.20% (PAHO, 2018), a situation that may force discontinuation of therapy in up to 48% of patients receiving NFX (Crespillo-Andujar et al., 2018a; Crespillo-Andujar et al., 2018b; Jackson et al., 2020). AEs include weight loss greater than 5-15%, digestive disorders (nausea, vomiting, diarrhea, epigastralgia and dyspepsia, abdominal distension), headaches, irritability, insomnia, mood disorders, memory loss, fever, arthralgias, myalgias, severe or significant skin and mucosal rashes such as Stevens-Johnson syndrome, evidence of thrombocytopenia, pancytopenia or signs of bone marrow depression, elevated transaminases, leukopenia below 2500/mm^3, CNS disorders such as paresis, paralysis or seizures, and behavioral changes, especially in the case of NFX.

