## 9.3. Study description:

This is a proof-of-concept Phase II clinical trial with three different groups: Two groups will receive antichagasic therapy plus 40 or 80 mg/day of ATO. The third group will receive a placebo plus antichagasic therapy. The placebo is justified as long as the patient receives the complete conventional antichagasic treatment; therefore, the management of his Chagas disease is assured. In this clinical trial, the placebo will be a nutritional supplement tablet with an appearance similar to that of ATO. This product was chosen given the potential difficulties in manufacturing a small number of pills since the trial does not have a pharmaceutical industry sponsor capable of manufacturing it under Good Manufacturing Practice standards.

Nutritional supplements do not affect vascular or cardiac inflammatory parameters and therefore do not introduce confounding elements in the comparative analysis with atorvastatin.

Patients will first receive conventional antichagasic therapy for two months. After two weeks (or until normalization of liver enzymes), treatment with atorvastatin or placebo will be initiated for

four months. These doses were chosen to minimize false negative results, thus providing the best hypothesis test and maximizing the pharmacodynamic effect on inflammation and cardiac and endothelial function. In addition, the treatment sequence aims to minimize adverse reactions that could be caused by the eventual combination of antichagasic drugs with atorvastatin. Study subjects will be randomized, and the three groups will be double-blinded (both clinical investigators and subjects will be blinded) to ATO or placebo. However, antichagasic therapy will be open-labeled. In addition, qPCR and the other laboratory evaluations, as well as ECGs and 2D echocardiograms, will be performed with the clinical investigators blinded to ATO or placebo allocation.

This study will be conducted in four centers: 1) Hospital San Juan de Dios and 2) Hospital Felix Bulnes in Santiago, Metropolitan Region, 3) Hospital [name] in Viña del Mar, 4) Hospital San Martin de Quillota, Valparaiso Region. Each center annually admits 60 new patients to its Chagas Control Program (CCP). These four centers are part of the care network of the National Chagas Disease Control Program.

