Finally, a baseline resting ECG and a 2D echocardiogram will be performed. Both tests will be performed at each center. The ECG should be normal or with nonspecific changes (incomplete right bundle branch block, incomplete left anterior fascicular block, mild bradycardia, minor PR interval widening, and minor ST-T changes). Any clinically significant abnormality found on the electrocardiogram will automatically lead to the exclusion of the patient from this study (see exclusion criteria).

After randomization and before starting treatments, patients will undergo a new focused physical examination, and blood will be drawn for qPCR and biomarker determination.

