#### **11.2.5. Withdrawal from the study:**

Patients will be considered to have withdrawn from the study if they have entered the study (i.e., given informed consent and received at least one dose of treatment) but have not completed the treatment phase of the study or the follow-up assessments after the EOT.

The following reasons may be considered to indicate patient withdrawal from the study: severe skin reactions or repeated moderate skin reactions; serum ALT greater than 3 X ULN at any time or serum

bilirubin elevation  $>2 \times \text{ULN}$ ; muscle weakness and increased CK  $> 1\text{ULN}$ ; SAE or severe; any condition that the clinical investigator or any other primary care physician not involved in the study deems medically necessary to discontinue treatment and withdraw a patient from the study; significant protocol deviation; loss to follow-up; retraction of informed consent by the patient; termination of the study by the investigator. If a subject fails to return for a scheduled visit, every effort should be made to contact the subject. In all circumstances, if possible, every effort should be made to document the subject's outcome. If the subject withdraws consent, no further evaluations should be performed, and no attempt should be made to collect additional data, except safety data, which should be collected if possible. Data obtained from withdrawn patients before the withdrawal will continue to be considered. Subjects drawn from this study will not be replaced.

Discontinuation of treatment does not imply withdrawal from the study. In these cases, treatment may be interrupted for a few days; therefore, treatment will be considered incomplete or delayed. Treatment with ATO and antichagasic drugs may be resumed according to the assessment of the clinical investigator in charge of the patient. These patients should continue with study visits and evaluations as scheduled.

Subjects withdrawn from the study will not be replaced.

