### **12.3. Populations to be analyzed:**

Three populations will be included in the analysis: i) the intention-to-treat (ITT) population comprising all patients randomized by their assigned treatment groups, ii) the per-protocol population comprising all ITT patients without any significant deviation from protocol, and iii) the safety population comprising all patients randomized and having received at least one dose of study treatment.

Descriptive statistics for demographic data and baseline characteristics will be presented for the per-protocol and ITT populations.

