### **12.5. Safety analysis:**

The proportion of patients presenting at least one AE will be described. The incidence rate and 95% confidence interval per study group will be presented. Otherwise, only descriptive statistics will be presented. Laboratory safety parameters (hematology and biochemistry) will also be described individually for each study group, showing the proportion of patients by degree of elevation relative to ULN and to baseline values and changes in blood levels over time.

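### Randomisation comes about 70-74 days or more before the first atorvastatin/placebo dose, so losses and adverse events on antichagasic therapy dilute the efficacy and safety comparisons

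*Protocol*

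**What the plan says.** - **Timing of randomisation.** The schedule in section 9.6 places it at visit 2, day 0. Section 9.5 counts the visits from there: "Once the patient is randomized and treatments are initiated, they will have follow-up visits during the treatment phase of the study". Section 9.7 confirms that it precedes all treatment: "After randomization and before starting treatments, patients will undergo a new focused physical examination".
- **Sequence.** Section 9.3: "Patients will first receive conventional antichagasic therapy for two months". Atorvastatin or placebo follows after two weeks, or later if liver enzymes have not normalised. Section 7.1.4 gives the antichagasic course as 60 days; section 9.5 gives eight weeks.
- **Analysis sets.** In section 12.3, ITT is everyone randomised, analysed as assigned. The third set is "the safety population comprising all patients randomized and having received at least one dose of study treatment". The term study treatment is not limited to atorvastatin or placebo.
- **Safety summary.** Section 12.5: "The proportion of patients presenting at least one AE will be described". Incidence per group with a 95% confidence interval follows. No split by treatment phase is stated.
- **Expected antichagasic toxicity.** Section 7.1.4 cites a mean 16.20% incidence of serious adverse events, "a situation that may force discontinuation of therapy in up to 48% of patients receiving NFX".
- **Withdrawal.** Section 11.2.5 lists, among possible reasons, "serum ALT greater than 3 X ULN at any time". Withdrawn subjects are not replaced.
- **Planning figures.** Section 12.1: 75 per group, 0.40 v 0.20, 90% power, two-sided 5%, raised to 100 per group for 25% dropout.

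**The concern.** For roughly the first ten weeks after randomisation the arms receive the same treatment, so nothing in that period can carry information about atorvastatin. It is also the period in which the protocol's own background section expects substantial toxicity and stopping of drug. Anyone lost then remains in the ITT denominator without having taken the randomised drug, and any adverse event then counts in the at-least-one-event proportion of the patient's group.

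Section 12.1 treats the 25% dropout as lost numbers: 100 are recruited so that 75 contribute at the full 0.40 v 0.20. Section 12.3 keeps all 100 in the primary analysis. To the extent that losses precede blinded drug, the contrast in that analysis is smaller than 0.20, and the inflation step does not allow for this. Safety belongs to the primary goal in section 8.1, so dilution of the adverse-event comparison matters as well.

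**Working it through.** **1. Delay from randomisation to first blinded dose**

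- 60-day wording (section 7.1.4; two months in section 9.3): 60 + 14 = 74 days.
- Eight-week wording (section 9.5): 56 + 14 = 70 days.
- Either is longer if liver enzymes take more time to normalise.

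**2. The plan's own figure**

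The normal approximation with pooled variance under the null is used throughout, two-sided 5% as in section 12.1:

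power = Φ{ [ |p₁ − p₀| − 1.96·√(2·p̄(1 − p̄)/n) ] / √[ (p₁(1 − p₁) + p₀(1 − p₀))/n ] }

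- n = 75, 0.40 v 0.20: (0.20 − 0.1467)/0.0730 = 0.730, so power is 77%, not the stated 90%. By the same method 90% needs 109 per group. This shortfall is a separate matter.
- The dropout step reproduces: 75/0.75 = 100.
- n = 100, 0.40 v 0.20, no loss: 88%. This is the reference below.

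**3. Dilution of the efficacy contrast**

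Let q be the share of randomised patients who never start blinded drug. The protocol does not give q; 10%, 15% and 25% are assumptions, and 25% is the planned total dropout.

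- Case A, non-starters respond at the placebo rate: p₁ = 0.40(1 − q) + 0.20q, p₀ = 0.20.
- Case B, non-starters count as non-responders: p₁ = 0.40(1 − q), p₀ = 0.20(1 − q).
- Starters only, from the same 300 patients: n = 100(1 − q) per arm at 0.40 v 0.20.

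Example, case A with q = 25%: p₁ = 0.35, p̄ = 0.275; (0.15 − 0.1238)/0.0622 = 0.421; power 66%.

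| q | A: rates | A: power | B: rates | B: power | Starters only: n per arm, power | Gain over A / B (points) |
|---|---|---|---|---|---|---|
| 10% | 0.38 v 0.20 | 81% | 0.36 v 0.18 | 82% | 90, 84% | 3.4 / 1.7 |
| 15% | 0.37 v 0.20 | 76% | 0.34 v 0.17 | 79% | 85, 82% | 5.5 / 2.6 |
| 25% | 0.35 v 0.20 | 66% | 0.30 v 0.15 | 72% | 75, 77% | 10.4 / 4.5 |

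The last column is the relevant one. The same patients are lost either way, so the fall from 88% overstates what a change of analysis set can recover.

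**4. Dilution of the adverse-event comparison**

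Let b be the chance of at least one event in the antichagasic phase and s the chance after blinded drug starts, taken as independent. Over the whole study the proportion is 1 − (1 − b)(1 − s), so a difference in s is multiplied by (1 − b). Neither b nor s is in the protocol; both are assumed, with s = 20% v 10%.

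| b | Atorvastatin v placebo, whole study | Gap (true gap 10 points) |
|---|---|---|
| 50% | 60% v 55% | 5 points |
| 70% | 76% v 73% | 3 points |
| 90% | 92% v 91% | 1 point |

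**The case against.** **The design may be deliberate.** Section 8.1 compares atorvastatin plus antiparasitic therapy with antiparasitic therapy alone and counts 12 months from the start of antichagasic treatment. An all-randomised analysis from day 0 answers that strategy question without bias. This stands, and is why that analysis should be kept. It does not remove the mismatch with section 12.1, which assumes an undiluted contrast.

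**Non-starters may be few.** A reader might take the 48% in section 7.1.4 as the share who never reach atorvastatin. The documents do not support that. It is a background figure for stopping nifurtimox. Section 11.1.1 allows a switch to benznidazole without withdrawal, section 11.2.5 says that discontinuing treatment is not withdrawal and only lists reasons that may be considered, and section 9.3 lets the gap lengthen until enzymes normalise. The true q is unknown and could be below 10%.

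**Safety.** Section 12.5 is descriptive and states no between-arm test that could lose power. Laboratory values are described over time, and section 11.2.4 uses timing in judging causality. A phase-split table could also sit in a statistical analysis plan that is not shown. All of this limits the safety part to how readable the any-event proportion is. The set definition and that summary are nevertheless fixed in the protocol, with no link to the blinded drug.

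**Baseline.** It might be inferred that a day-0 baseline mixes the antichagasic effect into the biomarker contrast. No section says which sample is the baseline, and an effect common to all arms cancels in expectation. What remains is a possible gain in precision from the day-60 sample.

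**Conclusion.** The point holds as dilution of moderate size. The documents fix randomisation at day 0, identical treatment for about 70-74 days or more, an all-randomised ITT and a safety set not tied to the blinded drug. For non-starter shares of 10% to 25%, defining the set by first blinded dose gains about 3 to 10 power points, or 2 to 4.5 if non-starters count as failures. The any-event gap between arms would shrink from 10 points to between 5 and 1. These sizes rest on the rates in section 12.1 and on assumed values of q, b and s.

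Three stronger readings are not supported:

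- That 74 days is a minimum: the eight-week wording gives 70.
- That the design hides or biases the statin's effect: losses before blinded drug are equal in expectation across arms while the blind holds.
- That a change would restore 88% power: that needs 100 starters per arm, and the same 300 patients would not supply them.

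**What to change.** 1. **Section 12.3:** define the primary efficacy set as all randomised patients who took at least one dose of blinded atorvastatin or placebo, analysed as assigned. Keep all-randomised ITT as a sensitivity analysis. Exclusion before the first blinded dose is independent of arm while the blind holds. Define the safety comparison set the same way.
2. **Section 12.5:** report adverse events separately for the antichagasic phase and from first blinded dose onward, and compare arms only in the latter.
3. **Biomarkers:** use the day-60 sample, already in the schedule, as a baseline covariate.
4. **Sections 7.1.4, 9.3 and 9.5:** reconcile the eight-week and the two-month/60-day wordings.

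This needs a protocol amendment and a reliable record of the first blinded dose, but no new visits or samples. The cost is that the primary result applies to patients who get through the antichagasic phase, and fewer are analysed than enrolled.

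Randomising at the end of the washout is an alternative, but a larger change. No visit is scheduled between days 60 and 120, so a contact would have to be added, and sections 9.5, 9.6, 12.1 and 12.2 would need amending as well. It also changes the randomised population.

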| STUDY DESIGN: This is a proof-of-concept Phase II clinical trial with three different groups: two groups will receive antichagasic therapy plus 40 or 80 mg/day of ATO, respectively. The third group will receive a placebo plus antichagasic therapy. Patients will first receive conventional antichagasic treatment for two months. After a washout of two weeks (or until normalization of liver enzymes), treatment with atorvastatin or placebo will be initiated for two months. These doses were chosen to minimize false negative results, thus providing the best hypothesis test and maximizing the pharmacodynamic effect on inflammation and cardiac and endothelial function. In addition, the treatment sequence aims to minimize adverse reactions that could be caused by the eventual combination of antichagasic drugs with atorvastatin. Study subjects will be randomized, and the three groups will be double-blinded (both clinical investigators and subjects will be blinded) to ATO or placebo. However, antichagasic therapy will be open-label. In addition, qPCR and the other laboratory evaluations, as well as ECG and 2D echocardiograms, will be performed with the clinical investigators blinded to ATO or placebo allocation.

As mentioned above, this study will be conducted at four centers: 1) Hospital San Juan de Dios and 2) Hospital Felix Bulnes in Santiago, Metropolitan Region, 3) Hospital [name] in Viña del Mar, and |

4) Hospital San Martin de Quillota, Valparaiso Region.

**ABSTRACT:** Cardiac complications, including heart failure and arrhythmias, are major causes of disability and death in Chagas disease (CD). We postulate that statins ameliorate vascular and cardiac inflammation in patients with chronic CD, contributing to the recovery of endothelial and cardiac function and thereby improving the efficacy of antichagasic therapy.

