**symptoms or signs of NFX intolerance, s/he can be switched to BZD without being withdrawn from the study.**

The ATO, placebo, and antichagasic drugs should not be used for purposes other than this trial.

At this point, it is necessary to indicate that if the patient manifests symptomatology suggestive of heart failure during follow-up visits, s/he will be referred to cardiological consultation for evaluation. The addition of specific therapy for managing heart failure will be recorded in the clinical record of the trial.

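### The only biomarker and qPCR sample in the statin phase is fixed at day 120 from randomisation, while the statin start can slip, so statin exposure at that sample varies from 46 days down to none

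*Protocol*

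**What the plan says.** **Visit calendar.** Section 9.5 of the protocol states that once treatment begins "they will have follow-up visits during the treatment phase of the study on days 30, 60, 120, and 180". The schedule tables in the Summary and in 9.6 use the same days, with baseline as day 0. Biomarkers are marked at days 0, 60, 120 and 360, and qPCR at screening and days 120 and 360 (9.7 adds a pre-treatment draw). ECGs are unconditional at screening and days 60, 120 and 360; those on days 180 and 240 are only for patients with an earlier abnormality. Echocardiography is at screening and day 360.

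**Statin start.** The Summary says: "After a washout of two weeks (or until normalization of liver enzymes), treatment with atorvastatin or placebo will be initiated for two months". Section 9.3 agrees on the start ("After two weeks (or until normalization of liver enzymes), treatment with atorvastatin or placebo will be initiated for") but then gives a course of four months. Section 9.5 gives the shorter course: "The administration of ATO and placebo will continue for an additional eight weeks in their respective groups".

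**What can delay the start.**
- The washout, which 9.5 describes as "with a two-week rest period or until normalization of liver enzyme levels", has no maximum.
- Section 11.2.5 allows interruptions of a few days and says "therefore, treatment will be considered incomplete or delayed"; these patients keep their planned visits.
- Section 11.1.1 lets a patient with nifurtimox (NFX) intolerance change to benznidazole (BZD): "symptoms or signs of NFX intolerance, s/he can be switched to BZD without being withdrawn from the study". It does not say whether a new course begins.

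No visit is tied to the first ATO/placebo dose.

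**The concern.** The trial tests whether a statin changes inflammation, endothelial activation and parasite response. Only one sample of those markers falls inside the statin phase. If its date is fixed while the start of statin can slip, patients with very different exposure share one visit label. Those sampled before the first dose, or just after it, cannot show much of a statin effect.

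At stake are the on-statin comparisons of biomarkers and qPCR (8.2.1, 8.2.3 and the additional measures (a), (c) and (d) in 9.1). Measure (d) in particular relates biomarker levels at each time point to the ATO regimen. Statistical analysis cannot recover a sample that was never drawn on treatment, so the schedule is the place to deal with this.

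**Working it through.** The plan gives no figure for statin exposure at day 120, so there is none to reproduce. The steps below use its own calendar, with two months taken as 60 days and four months as 120.

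**1. Nominal start.** 60 days of antichagasic drug + 14 days of washout = day 74.

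**2. Nominal end.**
- Eight-week course: 74 + 56 = day 130.
- Four-month course: 74 + 120 = day 194.

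**3. Samples inside the statin phase.** Of the biomarker days 0, 60, 120 and 360 and the follow-up qPCR days 120 and 360, only day 120 lies between day 74 and day 130 or 194. The next sample, day 360, comes 360 − 130 = 230 or 360 − 194 = 166 days after the last nominal dose. Day 120 is also the only unconditional ECG in the statin phase. Under the four-month course day 180 falls on statin too, but its ECG is conditional.

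**4. On-schedule exposure.** 120 − 74 = 46 days, or 42 to 50 with the ±4-day window. That is 46/56 = 82% of the eight-week course, with the sample 130 − 120 = 10 days before its end, or 46/120 = 38% of the four-month course.

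**5. Exposure with a delay of d days.** max(0, 46 − d):

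| Delay (days) | Statin start (day) | Statin days at day 120 |
|---|---|---|
| 0 | 74 | 46 |
| 7 | 81 | 39 |
| 14 | 88 | 32 |
| 28 | 102 | 18 |
| 42 | 116 | 4 |
| 46 or more | 120 or later | 0 |

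With a delay of 46 days or more, the patient has no biomarker or qPCR sample on statin unless the course runs to day 360.

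**6. Effect of a switch from NFX to BZD on day s.** Two assumptions bracket the gap in 11.1.1.
- A new 60-day course begins: start = s + 60 + 14, so exposure at day 120 = 46 − s. This gives 31 days for s = 15, 16 for s = 30, and none for s = 46 or later.
- Only the remaining days are completed: no delay, 46 days.

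**7. Direction of the effect.** The arms receive the same care until the first ATO/placebo dose, and allocation is blinded. Delay before that dose should therefore not depend on the arm. It pulls the on-statin contrast towards no difference and does not favour ATO.

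**The case against.** Several points on the other side are sound.

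- **Long delays are not shown to be common.** Pauses are of a few days; a 7-day pause leaves 39 statin days. A switch matters only if a course restarts. The listed withdrawal reasons include raised ALT, which may limit long washouts. A reader might infer that patients who switch, pause or have a longer washout reach day 120 with little or no atorvastatin. That needs a delay of about four to six weeks, and the documents give no frequency for it.
- **A power loss does not follow.** A reader might take the background statement that adverse events "may force discontinuation of therapy in up to 48% of patients receiving NFX" and apply it to the 0.40 versus 0.20 contrast in 12.1, giving 0.40 − 0.20 × 0.48 = 0.304 in the ATO arm. The documents do not support this. The 48% is an upper figure for stopping NFX, not for switching and restarting, and the share of patients on NFX is not given. Patients who leave are already in the 25% dropout allowance. The 0.40 and 0.20 refer to end of treatment (EOT) and include echocardiography, which is not done on day 120.
- **Day 120 is not named as the scored time point.** Sections 8.1 and 9.1 put the primary outcome at 12 months, and the biomarker test in 12.4 has no time point. How off-schedule samples are scored may properly be left to the statistical analysis plan.
- **The day count may be nominal.** Two months plus four months is 60 + 120 = day 180 only if the rest period is left out. If the visit days are treatment days without the washout, day 120 would mean 120 − 60 = 60 statin days. The design diagrams could not be read for this check and might settle it. The tables, however, count from baseline as day 0 and state no such convention.

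These points limit the size of the problem. They do not change the fact that, as written, the one on-statin biomarker and qPCR sample does not follow the statin start.

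**Conclusion.** The point holds as a scheduling weakness with a dilution effect. On the calendar as written, statin exposure at the only on-statin biomarker and qPCR sample is 46 days less any delay, from 46 days to none, and the plan allows delay without a limit. The result rests on a 60-day antichagasic course, a 14-day minimum washout and visits counted from day 0.

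The amount of dilution cannot be stated, because it depends on how often long delays occur. Loss of precision and a risk of a false-negative secondary result are the consequences; bias in favour of ATO is not expected. The 12-month primary outcome is not directly affected. It is worth correcting because the correction is cheap and must be made before the samples are drawn.

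**What to change.** In 9.5 and both schedule tables:

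- Time the present day-120 assessment from the first ATO/placebo dose, at a fixed interval that lies within the course, with the existing ±4-day window.
- Record the date of that first dose for every patient.
- Keep day 360 counted from day 0, so that the 12-month outcome is unchanged.
- Give patients who never start ATO/placebo the calendar day-120 visit, so that they stay in the intention-to-treat analysis. State how this applies to a patient still in washout on day 120, who may yet start.

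The sponsor must also reconcile three matters: the statin duration (two months or eight weeks in the Summary and 9.5, four months in 9.3); the status of day 180, which 9.5 lists both in the treatment phase and after EOT; and how switches, pauses and the washout move the statin start. No clinical rule is proposed here.

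The cost is a change of wording and one recorded date, with no added visits or samples. The downside is that the mid-study visit will fall on different calendar days from randomisation, which makes site scheduling less uniform.
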